### Women Only:

Date of last menstrual cycle: \_\_\_\_\_

Are you menstruating regularly?    ☐ Yes    ☐ No

Are you post-menopausal (natural or from surgery)?    ☐ Yes    ☐ No

### Family History

Has any first degree family member (child, parent, or sibling) had any of the following illnesses?

| Illness                 | Which family member? |
|-------------------------|----------------------|
| Anemia or Blood Disease |                      |

|                                              |  |
|----------------------------------------------|--|
| Cancer                                       |  |
| Diabetes                                     |  |
| Heart Disease                                |  |
| High Blood Pressure                          |  |
| Severe Mental Illness                        |  |
| Stroke                                       |  |
| Substance abuse (alcohol, tobacco, or other) |  |
| Other serious illness                        |  |

## Medications

Please list any medications you are allergic to:

|    |    |    |
|----|----|----|
| 1. | 2. | 3. |
|----|----|----|

Please list all medications you are now taking or have used in the last month (include over-the-counter drugs, vitamins, and especially prescriptions). It is okay to skip dates for long-term medications:

| Name of Medication | Dosage | Start Date | Stop Date | Prescribed for what problem? |
|--------------------|--------|------------|-----------|------------------------------|
| 1.                 |        |            |           |                              |
| 2.                 |        |            |           |                              |
| 3.                 |        |            |           |                              |
| 4.                 |        |            |           |                              |
| 5.                 |        |            |           |                              |
| 6.                 |        |            |           |                              |
| 7.                 |        |            |           |                              |
| 8.                 |        |            |           |                              |

Are you taking Linezolid or intravenous methylene blue? ☐ Yes ☐ No

Have you used monoamine oxidase inhibitors (MAOI) in the past 14 days? ☐ Yes ☐ No

Have you used experimental or investigational drugs in the past 30 days? ☐ Yes ☐ No

## Smoking Cessation Medications

For each of the following, mark if you have used the medication, experienced any side effects, allergy or intolerance with usage, or had to stop taking the medication due to side effects:

|                               | Not used              | Used                  | Side Effects | Stopped due to Side Effects? |                       |
|-------------------------------|-----------------------|-----------------------|--------------|------------------------------|-----------------------|
|                               |                       |                       |              | Yes                          | No                    |
| Nicotine Patch                |  |  |              |         |  |
| Nicotine Gum                  |  |  |              |         |  |
| Nicotine Lozenge              |  |  |              |         |  |
| Nicotine Inhaler              |  |  |              |         |  |
| Zyban (Wellbutrin, Bupropion) |  |  |              |         |  |
| Chantix (Varenicline)         |  |  |              |         |  |

Have you used any of these medications in the past 30 days? ☐ Yes ☐ No

## **Review of Systems**

### **General:**

- ☐ None of these apply
- ☐ Unexplained weight loss or gain
- ☐ Fever or chills
- ☐ Fatigue / lack of energy
- ☐ Weakness
- ☐ Trouble sleeping

### **Skin:**

- ☐ None of these apply
- ☐ Rashes
- ☐ Lumps
- ☐ Color change
- ☐ Hair and nail changes

### **Head:**

- ☐ None of these apply
- ☐ Headache
- ☐ Head injury

### **Ears:**

- ☐ None of these apply
- ☐ Decreased hearing
- ☐ Earache
- ☐ Ringing in the ears

### **Eyes:**

- ☐ None of these apply
- ☐ Vision problems
- ☐ Specks
- ☐ Blurry or double vision
- ☐ Flashing lights
- ☐ Redness
- ☐ Pain

### **Nose:**

- ☐ None of these apply
- ☐ Stuffiness
- ☐ Discharge
- ☐ Itching
- ☐ Sinus pain
- ☐ Nose bleeds

### **Throat:**

- ☐ None of these apply
- ☐ Teeth/gum problems
- ☐ Dentures
- ☐ Hoarseness
- ☐ Sore tongue
- ☐ Dry mouth
- ☐ Sore throat
- ☐ Thrush
- ☐ Non-healing sores
- ☐ Difficulty swallowing

### **Neck:**

- ☐ None of these apply
- ☐ Lumps
- ☐ Stiffness
- ☐ Pain
- ☐ Swollen glands

### **Respiratory:**

- ☐ None of these apply
- ☐ Cough (dry or wet, productive)
- ☐ Shortness of breath
- ☐ Coughing up blood
- ☐ Painful breathing
- ☐ Wheezing

### **Cardiovascular:**

- ☐ None of these apply
- ☐ Chest pain or discomfort
- ☐ Tightness
- ☐ Heart
  - pounding/fluttering/  
palpitations
- ☐ Difficulty breathing lying down
- ☐ Swelling
- ☐ Shortness of breath with activity
- ☐ Suddenly awaking from sleep
  - with shortness of breath

### **Gastrointestinal:**

- ☐ None of these apply
- ☐ Swallowing difficulties
- ☐ Heartburn
- ☐ Constipation
- ☐ Vomiting
- ☐ Change in bowel habits
- ☐ Rectal bleeding
- ☐ Diarrhea
- ☐ Stomach pain
- ☐ Yellow eyes or skin
- ☐ Change in appetite
- ☐ Nausea

**Urinary:**

- ☐ None of these apply
- ☐ Frequency
- ☐ Urgency
- ☐ Blood in urine
- ☐ Pain with urination
- ☐ Change in urinary strength
- ☐ Incontinence

**Vascular:**

- ☐ None of these apply
- ☐ Calf pain with walking
- ☐ Leg cramping
- ☐ Leg pains

**Musculoskeletal:**

- ☐ None of these apply
- ☐ Muscle or joint pain
- ☐ Stiffness
- ☐ Back pain
- ☐ Swelling of joints
- ☐ Trauma

**Neurologic:**

- ☐ None of these apply
- ☐ Dizziness
- ☐ Fainting
- ☐ Tingling
- ☐ Weakness
- ☐ Numbness
- ☐ Tremor
- ☐ Shaking episodes

**Hematologic:**

- ☐ None of these apply
- ☐ Bruise easily
- ☐ Bleed easily

**Endocrine:**

- ☐ None of these apply
- ☐ Heat or cold intolerance
- ☐ Sweating
- ☐ Frequent urination
- ☐ Thirst
- ☐ Change in appetite

**Psychiatric:**

- ☐ None of these apply
- ☐ Nervousness
- ☐ Memory loss
- ☐ Feeling down

**Females only**

- ☐ None of these apply
- ☐ Pregnant or currently breast feeding

## Appendix 2: Smoking History

*Please answer the following questions are about your history of smoking, use of other products and medications.*

1. How many cigarettes have you smoked per day, on average? \_\_\_\_\_ [1-99]
2. How many years have you smoked? \_\_\_\_\_ [1-99]
3. Do you usually smoke menthol or non-menthol cigarettes?
  - 1 = Non-Menthol
  - 2 = Menthol
  - 3 = Both
  - 0 = Don't know
4. Which of the following tobacco products have you used in the last week? (Check all that apply)
  - 1 = Cigarettes
  - 2 = Cigars
  - 3 = Pipes
  - 4 = Hookah
  - 5 = Cigarillos
  - 6 = E-cigarettes
  - 7 = Chewing tobacco
  - 8 = Snuff
  - 9 = Other
5. During the last week did you use any of the following drugs? (Check all that apply)
  - 1 = Marijuana
  - 2 = Cocaine/Crack
  - 3 = Meth
  - 4 = PCP
  - 5 = Heroin
  - 6 = Opioids such as Morphine, Oxycotin, Percocet, Vicodini, Fentanyl
  - 7 = Benzodiazepines such as Valium, Xanax, Klonopin
  - 8 = Other

## Appendix 3: Financial Questions

*These next 10 questions are about your finances, medical coverage, and benefits.*

1. What is your Gross Yearly Income (include all forms of income)?
  - 1= Less than \$10,000
  - 2= \$10,000 – \$24,999
  - 3= \$25,000 – \$49,999
  - 4= \$50,000 – \$74,999
  - 5= \$75,000 – \$99,999
  - 6= Over \$100,000
  - 0 = Don't know
  
2. What is your means of paying for medical services? (Check all that apply)
  - 1 = Private Insurance: HMO, PPO, CMO
  - 2 = Medicare
  - 3 = Medicaid
  - 4 = Veteran's Benefit
  - 5 =No insurance
  - 6 = Other
  - 7 = Don't know
  - 8= Not retired
  
3. Which one of the following statements best describes your personal financial situation?
  - 1 = I am in good shape. I am able to save and plan for the future.
  - 2 = I am okay. I am saving a little and I am able to provide for my needs.
  - 3 = I am barely getting by. I have to budget carefully and am not able to plan for the future.
  - 4 = I am falling behind. I have to use savings or go further into debt to pay my bills.
  - 5 = I am in serious financial trouble and can't quite see how I am going to make it.
  - 0 = Don't know
  
4. What is the highest grade or year of school you completed?
  - 1= Less than high school
  - 2= GED
  - 3= High School
  - 4= Some college, but no degree
  - 5= Associate's Degree (2 year degree)
  - 6= Bachelor's degree (4 year degree)
  - 7= Graduate education

## Appendix 4: Cost of Smoking

*These next questions are about the cost of cigarettes to you.*

1. How do you usually buy your cigarettes?
- 1 = By the Pack
  - 2 = By the Carton
  - 3 = Individually
  - 0 = Don't know

|                                                                                     |
|-------------------------------------------------------------------------------------|
| IF 1 = go to Question 43a
IF 2 = go to Question 43b
IF 3 = go to Question 43c |
|-------------------------------------------------------------------------------------|

- 1a. How much did you pay for the LAST PACK of cigarettes you bought?

\$ \_\_\_\_ . \_\_\_\_ \$1.00-\$10.00)

- 1b. How much did you pay for the LAST CARTON of cigarettes you bought?

\$ \_\_\_\_ . \_\_\_\_ (\$1.00 – \$99.00)

- 1c. How much did you pay for the LAST CIGARETTE you bought?

. \_\_\_\_ ¢ ( 0-99¢ )

|                                                                                                                                |
|--------------------------------------------------------------------------------------------------------------------------------|
| 44. Calculate: Cost of 1 cigarette: (Pack holds 20 cigs – so divide by 20) (Carton holds 200 so divide by 200) (do not report) |
|--------------------------------------------------------------------------------------------------------------------------------|

|                                                                                    |
|------------------------------------------------------------------------------------|
| 44a. Calculate Cigs per day x cost of each cig = Cost per day. Report Cost per day |
|------------------------------------------------------------------------------------|

|                                                                       |
|-----------------------------------------------------------------------|
| 44b. Calculate Cost per week = cost per day x 7. Report cost per week |
|-----------------------------------------------------------------------|

|                                                                          |
|--------------------------------------------------------------------------|
| 44c. Calculate Cost per month = cost per day x 30. Report cost per month |
|--------------------------------------------------------------------------|

|                                                                          |
|--------------------------------------------------------------------------|
| 44d. Calculate Cost per year = Cost per day x 365. Report cost per year. |
|--------------------------------------------------------------------------|

## Appendix 5: Medication Intolerance Questions

*The next questions will help us determine which medications might be appropriate for you.*

1. Are you willing to use the Nicotine Patch?  
1 = I am willing to use  
2 = I would consider using it  
0 = Don't know
2. Are you willing to use nicotine gum or nicotine lozenge?  
1 = I am willing to use  
2 = I would consider using it  
0 = Don't know  
IF male, skip questions 3&4.
3. Which best describes any potential plans to get pregnant?  
1 = Not applicable (post-menopausal, hysterectomy)  
2 = I am pregnant now  
3 = I hope to get pregnant in the next 12 months  
4 = I hope not to get pregnant in the next 12 months
4. Are you currently nursing?  
1 = YES  
2 = NO
5. Have you been diagnosed with any of the following conditions? (Check all that apply)  
1 = Schizophrenia  
2 = Bipolar Disorder  
3 = Closed Angle Glaucoma  
4 = Brain Cancer or Cerebral Aneurysm  
5 = Stroke  
6 = Seizure  
0 = I have none of these conditions
6. Do you currently take anti-seizure medications such as Dilantin, Keppra, Depakote, Tegretol, Lyrica, Topamax, or Lamictal?  
1 = YES  
2 = NO  
0 = Don't know
7. Do you currently take an MAO Inhibitor such as Linezolid, Isoniazid, Selegiline, Rasagiline, Isocarboxazid, Phenelzine, or Tranylcypromine?  
1 = YES  
2 = NO  
0 = Don't know
8. Are you willing to use Chantix (varenicline)?  
1 = I am willing to use  
2 = I would consider using it  
0 = Don't know
9. Are you willing to use Wellbutrin (bupropion)?  
1 = I am willing to use  
2 = I would consider using it  
0 = Don't know

## Appendix 6: Health and Surgery

*The next several questions are about your health.*

1. Are you planning to have surgery?
  - 1= I am not scheduled for surgery and do not think I will need surgery in the future.
  - 2= I am scheduled for surgery
  - 3= I will probably need surgery, but it is not scheduled
  - 4 = Other

IF the answer to 1 = 2, ask question 2.

2. What is the date of the scheduled surgery \_\_\_\_\_

## Appendix 7: Cancer Questions

*The next questions are about cancer diagnosis and treatment*

1. Are you currently undergoing diagnosis, treatment, or follow up for cancer or possible cancer?
  - 1 = Yes
  - 2 = No

## Appendix 8: Demographics

*These next three questions are about you.*

1. What is your race?
  - 1 = American Indian or Alaskan Native
  - 2 = Asian
  - 3 = Black or African American
  - 4 = Native Hawaiian or Pacific Islander
  - 5 = White
  - 6 = Other
  - 0 = Don't know
2. Do you consider yourself to be Hispanic or Latino?
  - 1=YES
  - 2=NO
  - 0 = Don't know
3. What is your gender?
  - 1= Male
  - 2= Female

## **Appendix 9: Alcohol Use Disorders Identification Test (AUDIT-C)(Bush, Kivlahan, McDonell, Fihn, & Bradley, 1998)**

The next questions are about your alcohol use.

1. How often do you have a drink containing alcohol?

0= Never

1= monthly or less

2= 2-4 times a month

3= 2-3 times a week

2. How many standard drinks containing alcohol do you have on a typical day?

0= 1 or 2

1= 3 or 4

2= 5 or 6

3= 7 to 9

4= 10 or more

3. How often do you have six or more drinks on one occasion?

0 = Never

1 = Less than monthly

2 = Monthly

3 = Weekly

4 = Daily or almost daily

4. Calculate: Add all scores of 3 question above together.

Then reference score to gender:

3 or higher for females = likely alcohol abuse or dependence

4 or higher for males = likely alcohol abuse or dependence

## Appendix 10: Drug Use Question

1. How many times in the past year have you used an illegal drug or used a prescription medication for non-medical reasons? \_\_\_\_\_

## Appendix 11: Recent Smoking

*The follow questions are about your recent smoking*

1. In the last 7 days, have you smoked at all - even a puff?  
1=YES  
2 = No  
0 = Don't know
2. In the last 7 days, how many cigarettes have you smoked per **day**?  
  
\_\_\_\_\_ [0-99]
3. In the last 30 days, have you smoked at all- even a puff?  
1= YES  
2 = No
4. On average, how many cigarettes have you smoked per day over the last 30 days?  
\_\_\_\_\_

**Adherence questions- These questions will be used for phone-based assessments. Medication adherence for in-person visits will be assessed via diaries, which is found in Appendix 20.**

(CTA Dialogue)

Medications that have been given to you for this study should be taken as follows

- Patch: put on in AM and wear for 24 hours unless otherwise directed
- Study pills: are each taken two times per day, in the morning and in the evening unless otherwise directed by study personnel

1. Did you choose to use the nicotine patch or varenicline?

1= Nicotine Patch

2= Varenicline

If "Nicotine Patch" selected ,go to questions 1a-1c.

If “Varenicline” selected, go to questions 2a-2c

1a) Over the last seven days, how many days have you used the nicotine patch as prescribed?

1b) Over the last seven days, how many days have you used the pills as prescribed?

1c) If answer to 1a or 1 b is less than 7 (100% adherence), please provide reason why you did not follow the directions above.

2a) Over the last seven days, how many days have you taken the varenicline pills as prescribed above?

2b) Over the last seven days, how many days have you taken the bupropion pills as prescribed above?

2c) If answer to 2a or 2b is less than 7 (100% adherence), please provide reason why you did not follow the directions above.

## Appendix 12: Work Questions

*The next few questions are about work.*

1. Please describe your employment status. Are you currently...?

=

1 = Working full-time (21-40 hours per week)

2 = Working Part-time (20 hours per week or less)

3 = Unemployed and looking for work

4. Disability or medical leave

5 = Retired

6 = Other

7 = Don't know

2. If you work, how many days of work have you missed due to illness in the past 30 days?

\_\_\_\_\_ Days [1-30]

3. If you work, how many smoke breaks do you take during a typical workday?

\_\_\_\_\_ Breaks (0-9)

4. How long, on average, does each smoke breaks last? \_\_\_\_\_ (0-60 minutes)

## Appendix 13: Predictor Questions

1. On a scale from 1 to 7 where 1 is “not at all confident” and 7 is “extremely confident,” how confident are you that you can quit?

16

Not at all  
confident

Extremely  
confident

1

2

3

4

5

6

7

2. On a scale from 1 to 7 where 1 is “not at all” and 7 is “a lot,” how much do you want to quit?

Not at  
all

A lot

1

2

3

4

5

6

7

3. Calculate: Add scores of questions above together.

2-5 = Low Efficacy

6-10 = Moderate Efficacy

11-14 = High Efficacy

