#### **Exploratory Objectives**

6. The following baseline self-report assessment outcomes will predict biochemically confirmed 30-day continuous abstinence at 12 weeks post TQD and 7-day point prevalence abstinence at 2- and 12-weeks post-quit: nicotine dependence, depression, anxiety, stress, alcohol use, drug use, motivation, and self-efficacy.
7. The following baseline self-report assessment outcomes will predict lower number of cpd and higher number of days abstinent at 2- and 12- week visits: urge, withdrawal symptoms, depression, anxiety, stress, alcohol use, drug use, motivation, and self-efficacy.
8. The following baseline self-report assessment outcomes will predict abstinence on phone-based self-report at 1, 2, 6, 12, 26, and 52 weeks post-TQD urges, withdrawal, motivation to quit smoking or remain abstinent, and confidence in ability to quit or remain abstinent
9. Baseline scores on anxiety, depression, and stress will moderate the effect of allocation to Non-Responder status in the adaptive and standard treatment arms. This finding will show that poor response to pharmacotherapy may be related to high levels of anxiety, depression, or stress.
10. A prospective economic analysis of adaptive vs standard treatment will show cost-benefit outcomes from the perspective of people that smoke cigarettes, healthcare systems, insurance companies, and employers.
11. **Feasibility:** Demographics of patients at DSCP and Duke CSC will reflect the recruitment area
12. **Feasibility:** Medications used will show wide variation of use.
13. **Feasibility:** Attendance at DSCP Return Appointments will be favorable.
14. **Feasibility:** Referral Routes to DSCP will reflect recruitment area.
15. **Feasibility:** Medication side effects will be favorable.
16. **Feasibility:** Medication adherence will be favorable.

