### 9.1 Inclusion Criteria (assessed by research staff and/or study medical provider)

1. Age 18 years or older
2. Actively smoking 5 or more cigarettes per day for at least one year
3. Have a median CO of at least 7 ppm (on carbon monoxide breath test)
4. Willing to set a quit date within 6 weeks
5. Willingness to take Varenicline OR nicotine patch (patient choice) and Bupropion
6. Access to a telephone

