### **10.7.4. Subject-Rated Non-Standardized Measures to Be Collected at All Clinic Visits**

Thirty- and 7-day point prevalence are assessed in Recent Smoking (Appendix 11), as well as compliance with prescribed medications and reasons for non-compliance, if applicable.

A participant's employment status is assessed by Work Questions (Appendix 12); this measure also allows the study staff to calculate the amount of time spent during smoke breaks during the work day.

A participant's self-efficacy and motivation to stop smoking are assessed with Predictor Questions (Appendix 13).

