### **Confidence in Ability and Motivation to Become Tobacco-Free**

1. On a scale of 1-10, how motivated are you to quit smoking or stay quit if abstinent?

- |                         |                         |
|-------------------------|-------------------------|
| 1. Not at all motivated | 6.                      |
| 2.                      | 7.                      |
| 3. A little motivated   | 8. Very motivated       |
| 4.                      | 9.                      |
| 5. Moderately motivated | 10. Extremely motivated |

2. On a scale of 1-10, how confident are you that you can quit if abstinent or stay quit if abstinent?

- |                         |                         |
|-------------------------|-------------------------|
| 1. Not at all confident | 6.                      |
| 2.                      | 7.                      |
| 3. A little confident   | 8. Very confident       |
| 4.                      | 9.                      |
| 5. Moderately confident | 10. Extremely confident |

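### Appendix 13 scores self-efficacy as confidence plus desire to quit, which mixes two predictors the protocol lists separately, and the phone confidence item has no branch for a person still smoking

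*Protocol*

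**What the plan says.** Appendix 13 contains two items, each on a 1 to 7 scale. The first asks "how confident are you that you can quit" and the second asks "how much do you want to quit". The scoring line reads "3. Calculate: Add scores of questions above together". The total is banded: "2-5 = Low Efficacy", with 6 to 10 as Moderate and 11 to 14 as High. No separate motivation score is defined there.

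Section 10.7.4 assigns both constructs to this pair of items: "A participant's self-efficacy and motivation to stop smoking are assessed with Predictor Questions (Appendix 13".

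In section 3.1, exploratory hypothesis 6 lists the baseline predictors of abstinence as "nicotine dependence, depression, anxiety, stress, alcohol use, drug use, motivation, and self-efficacy". Hypothesis 7 again names motivation and self-efficacy as two entries. Section 13.5.1 lists the self-efficacy questions among potential moderators and self-efficacy among potential mediators.

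Section 9.1 requires participants to be "Willing to set a quit date within 6 weeks".

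The phone script in Appendix 19 measures motivation and confidence as two separate 1 to 10 items, which are not added. Its confidence item asks "how confident are you that you can quit if abstinent or stay quit if abstinent".

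**The concern.** A variable called self-efficacy should move with confidence. The Appendix 13 total moves equally with desire to quit, which the protocol elsewhere treats as a different predictor. If the total or its bands were used as self-efficacy, an association with abstinence could not be attributed to confidence rather than motivation. A moderator or mediator finding for self-efficacy would carry the same ambiguity. The bands add a second difficulty, because a person with no confidence at all is kept out of the Low band once desire is high enough.

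The phone item is a separate matter. Objective 8 in section 3.1 wants confidence in quitting, or in staying abstinent, compared at six time points up to week 52. As printed, both halves of the question are conditioned on being abstinent, so a participant who is still smoking is given no half that applies.

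**Working it through.** **Inputs.** From Appendix 13: confidence c and desire d, each an integer from 1 to 7; total T = c + d; Low if T is 2 to 5, Moderate if 6 to 10, High if 11 to 14. The distribution of desire is not in the protocol, so it is treated as an assumption and varied.

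**Reproducing the protocol's range.** The minimum total is 1 + 1 = 2 and the maximum is 7 + 7 = 14. This agrees with the bands, which cover 2 to 14 without gaps.

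**Counting the bands over all 7 × 7 = 49 answer pairs.**
- Low requires c ≤ 5 − d. That gives 4, 3, 2 and 1 values of c for d = 1, 2, 3 and 4, and none for d ≥ 5. Total: 4 + 3 + 2 + 1 = 10.
- High requires c ≥ 11 − d. That gives 1, 2, 3 and 4 values of c for d = 4, 5, 6 and 7. Total: 10.
- Moderate: 49 − 10 − 10 = 29.

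**Effect of desire on the Low band.** With d ≥ 5 the smallest total is 1 + 5 = 6, so Low is unreachable in all 3 × 7 = 21 pairs. With d = 7 the smallest total is 8.

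**Same confidence, different band.**

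| Confidence | Low if desire is | Moderate if desire is | High if desire is |
|---|---|---|---|
| 1 | 1–4 | 5–7 | never |
| 4 | 1 | 2–6 | 7 |
| 7 | never | 1–3 | 4–7 |

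The opposite profiles c = 1, d = 7 and c = 7, d = 1 both give T = 8, Moderate.

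**How often Low might occur (assumption, shown as a range).** For illustration, take the two items as independent, each distributed as 1 + Binomial(6, p), with mean confidence varied from 5.2 down to 2.8. P(Low) is the sum of P(c)·P(d) over pairs with c + d ≤ 5.

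| Assumed mean desire | P(Low), mean confidence 5.2 | P(Low), mean confidence 2.8 |
|---|---|---|
| 5.8 | 0.04% | 1.7% |
| 5.2 | 0.2% | 5.5% |
| 4.0 | 1.3% | 22% |

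**Phone item.** No arithmetic applies. The adjacent motivation question has one branch for quitting smoking and one for staying quit if abstinent. The confidence question attaches the abstinence condition to both branches. Objective 8 in section 3.1 describes the construct with both groups in view. The printed confidence wording therefore disagrees with the objective and with its neighbouring item.

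**The case against.** The strongest reply is that nothing is lost. The two items are asked and answered separately, section 13.5.1 speaks of self-efficacy questions rather than of a total, and no section says that the sum or the bands must enter a model. The derivation of an exploratory variable may properly sit in an analysis plan that is not shown. This stands as far as it goes: a reader might infer that self-efficacy and motivation cannot be separated in this trial, and that is true only of the total and its bands. The remaining problem is that Appendix 13 does fix a scoring rule, it is the only one given, and no other text in the protocol overrides it.

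A second reply is that the two harms work against each other. If desire is close to constant, the total is roughly confidence plus a constant and confounds little. If desire varies, the Low band need not be empty. This is fair, and the two effects should not be added together. But one or the other applies: with a ceiling on desire the bands fail, and with variation in desire the total confounds.

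A third reply is that willingness to set a quit date is not a minimum desire rating. That is correct. A reader might infer that the Low band is empty by construction, or that almost nobody in the trial could fall in it. The protocol does not support this, because 10 of the 49 pairs are Low and the distribution of desire is not stated. Nor does it single out low confidence as the group of interest for relapse: the sub-population paragraph in section 3.2 names dependence, depression, anxiety and stress.

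On the phone item, the wording looks like a slip with a plain intent, and callers or participants may correct it as they speak. It would therefore go too far to call answers from smokers and abstainers not comparable. The script is still wrong as printed.

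**Conclusion.** The point holds as a minor one. Followed as written, Appendix 13 produces a variable labelled Efficacy that is half desire to quit by construction, in a protocol that lists self-efficacy and motivation as distinct predictors. Two findings need no assumption: opposite profiles share the score 8, and Low cannot occur at desire 5 or above (0 of 21 pairs, against 10 of 49 overall). How rare Low would be does rest on an assumption. Scarcity is plausible in people who agree to set a quit date, but the illustration runs from 0.04% to about 22% across mean desire of 5.8 down to 4.0.

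The phone confidence item is a separate wording error with an evident intended meaning.

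The reach is limited to exploratory predictor, moderator and mediator analyses. The primary endpoint, the secondary smoking outcomes and the sample size are unaffected.

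**What to change.** In Appendix 13, delete the summed score and its Efficacy bands. State that item 1 alone is self-efficacy and item 2 alone is motivation, each analysed on its 1 to 7 scale wherever the protocol uses these constructs as predictor, moderator or mediator.

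In Appendix 19, reword the phone confidence item to end: 'that you can quit if smoking, or stay quit if abstinent'. Flag answers collected under the present wording so that they can be identified in the comparisons over time.

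The cost is small. Both Appendix 13 items are already collected separately, so no new data are needed. The phone change is one word in the script, plus a marker for calls made before it.
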